## Materials and methods

### Study design

An open-label, two-armed, assessor-blind, randomized controlled trial will be conducted. Randomization will be done by the principal applicant using a computer-generated random sequence. Participants will be randomly allocated to the IVR-CST or conventional CST group. The assessor will be blinded to condition allocation. Both the assessor and the participants will be reminded not to talk about issues related to treatment when they meet. The treatment protocol (version 1.0, dated March 3, 2025), which contains items from the World Health Organization Trial Registration Data Set, has been registered in ClinicalTrials.gov (NCT06838494). We will inform the funding agency, the Institutional Review Board of the Hong Kong Polytechnic University, ClinicalTrials.gov, and the publisher of the protocol of any amendments to the protocol. The experimental design is summarized in Fig 1.

**Fig 1 pone.0330686.g001:**
[figure not shown]
SPIRIT schedule. SPIRIT schedule illustrating the study design.

### Participants

A total of 66 community-dwelling participants with MCI will be recruited from community centres for the elderly and Non-Governmental Organizations (NGOs) providing care services to elderly people with cognitive impairment in different districts in Hong Kong. The proposed sample size is calculated using G*power 3.1.9.4, based on a power estimate of 80% with α = .05, an effect size of d = 0.40 (with reference to the averaged effect size of 0.43 on global cognition, as reported in the latest Cochrane Review [9] on cognitive stimulation on PwD), and an attrition rate of 25%. The effect size of cognitive stimulation on PwD ranged from 0.3 to 1.32 [9], while an effect size of 0.564 was reported in adapted CST on MCI [16]. Also, the effect size of previous RCTs using VR on cognitive intervention of MCI ranged from 0.6 to 0.9 on measures of general cognition. Thus, an effect size estimate of 0.4 for the current proposal is considered relatively conservative. The attrition rates of previous VR studies on MCI are considered low (6–14%); thus, the estimated attrition rate of the current proposal is considered modest.

Inclusion criteria include: 1) elderly aged 60 years or above. 2) A score of 16–21 out of 30 in the Hong Kong Brief Cognitive Test [25], with upper and lower cutoff scores for MCI as suggested by the test. 3) ability to speak and comprehend Cantonese; 4) normal or corrected-to-normal vision and hearing; 5) absence of physical illness/disability to prevent them from IVR-CST participation; and 6) compatible with IVR exposure in the 10-minute IVR trial without major signs of cybersickness, based on the symptoms given in the Simulator Sickness Questionnaire [26]. Exclusion criteria include 1) concurrent participation in other clinical therapy trials; 2) incompatibility with IVR exposure such as complaints of nausea, headache, or other severe discomforts during trial use; 3) a diagnosis of dementia or other psychiatric/neurological diseases such as depression, stroke, brain trauma, Parkinson’s disease; 4) hearing/visual/upper limb impairments that hinder CST/IVR-CST participation; 5) prior CST treatment; 6) Use of medication for MCI/dementia, e.g., aducanumab. Screening will be done by a trained research assistant in a quiet room. Participants’ demographic information, medical and family history will be obtained.

### Assessment and treatment schedule

All participants will be assessed at three time points throughout the study: week 1, week 9, and week 13 to evaluate their performance before, immediately after, and in the maintenance phase, respectively. The treatment schedule will be the same for both treatment conditions, in which 14 therapy sessions will occur twice per week from week 2 to week 8.

### Outcome measures and procedures

Primary outcomes: 1) The Hong Kong Montreal Cognitive Assessment (HK-MoCA; 27). It is a sensitive cognitive measure for MCI [27] and covers different cognitive domains, including visuo-spatial skills, executive functions, attention, memory, language, and orientation. The total score (out of 30) will be used to reflect global cognition; 2) Digit span forward and backward tasks, measures of working memory that predict progression from MCI to dementia [28]; 3) Verbal fluency of semantic category. Verbal fluency, which reflects semantic integrity, cognitive flexibility, and executive function, serves as a sensitive task in detecting MCI [29] and predicting conversion to dementia [30]. The number of items correctly produced in one minute in different semantic categories (animals, fruits, and transportation) will be tested.

Secondary outcomes: 1) Chinese version of the Modified Barthel Index [31], which assesses one’s level of independence in activities of daily living such as grooming, feeding, mobility, toileting, etc.; 2) The Hong Kong Lawton Instrumental Activities of Daily Living Scale [32], which evaluates the level of independency in performing community-living skills including cooking, household management, shopping, etc.

Feasibility outcome and users’ experience: Objective and quantifiable feasibility outcomes, including the number of adverse events and technical issues that occurred during intervention, and the level of adherence (actual duration and number of sessions conducted vs. scheduled) to the intervention protocol of both treatment groups, will be measured. Participants of the IVR-CST group will also attend a 20-minute semi-structured interview conducted post-therapy on topics including levels of comfort, presence of adverse effects such as cybersickness, and impact of therapy on daily functions.

Eye-tracking data obtained from the IVR-CST group will serve as an exploratory outcome. In each of the sessions, areas of interest (AOI) of the stimuli presented will be identified. For example, the childhood snacks or toys presented in the themed session ‘Childhood’ will be regarded as AOI. Parameters, including the number of fixations, duration of fixation, and number of revisits on the AOI generated by each participant, will be recorded in the HMD.

The above-mentioned assessment will be done by a trained research assistant with a healthcare background (e.g., rehabilitation science) who has no knowledge of the therapy condition of the subjects, and the whole process will be audio-taped.

### Treatment materials and procedures

In the IVR-CST group, a total of 14 IVR-CST sessions will be carried out twice per week, with each session lasting about 45 minutes. Therapy will take place in a quiet room in the community elderly centres. A research personnel who is a healthcare professional (e.g., occupational or speech therapist) with a certified CST facilitator qualification will be the group facilitator, and three to four participants with MCI will receive IVR-CST as a group throughout the sessions. An assistant will also be present to provide help if necessary. Treatment instruments will include commercially available HMDs with eye- and hand-tracking functions available (e.g., Meta Quest Pro) for each participant. Treatment materials (i.e., content to be delivered in each themed session) will be adapted from the Chinese-translated manual of CST [11]. Materials presented via HMD will include commercially available VR games suitable for the elderly, photo-real panoramic (i.e., 360-degree) images or videos, and two- or three-dimensional animated images and photos. Use of hand controllers or hand movement will be allowed in some activities, such as physical games or manipulation of 3D objects. Similar to the original CST manual, two activities with varying levels of difficulty will be available to allow some flexibility. The major difference between the level of difficulty of the currently proposed vs. the existing manual lies in the complexity of the tasks or the use of less familiar stimuli. For example, in session 10 ‘Orientation’. The original manual suggests the use of familiar local places as stimuli for discussion; in IVR-CST, less familiar places like overseas tourist spots will be introduced. Sample themed activities are given in Table 1. Treatment procedures will follow the Chinese-translated manual of CST [12]. In the first 10 minutes, participants and the facilitator will greet and meet, and sing-along a group song or share some snacks/drinks. Reality orientation will be followed by telling the participants the time, weather, and recent news/affairs. Then the facilitator will assist the participants to wear the HMD for about 30 minutes, during which the themed activity will be conducted. All participants will be seated comfortably and at a distance far enough from one another to ensure safety during hand movement during IVR exposure. According to the IVR-CST manual, the facilitator will guide the participants to conduct a range of activities, discussions, or sharing. Material presentation will be controlled by the facilitator via a laptop. S/he will not wear an HMD so that immediate assistance to the participants can be provided. In the last five minutes, the HMD will be taken off while the facilitator will round up the session. In the conventional CST group, the same treatment activities, materials, and procedures will be used, while photos, pictures, or real objects will be presented.

**Table 1 pone.0330686.t001:** Examples of themed activities of IVR-CST and conventional CST.

Session	Theme	IVR-CST	Conventional CST
1	Physical games	Level 1: IVR games requiring simple hand movement (e.g., fishing, ball throwing) Level 2: IVR games requiring more complex hand movement (e.g., coordination of both hands, playing darts)	Level 1: Tabletop games requiring simple hand movement (e.g., ball throwing to play tic-tac-toe) Level 2: Tabletop games requiringmore complex/refined upper limb movement (e.g., playing darts)
2	Sound	Level 1: Guessing game in which unfamiliar sounds or songs will be played. Level 2: Music sandbox game to create a song/rhythm via playing different musical instruments via limb detection/hand controller via VR.	Level 1: Guessing game in which unfamiliar sounds or songs will be played. Level 2: Music sandbox game to create a song/rhythm via playing different musical instruments provided onsite.
6	Faces/scenes	Level 1: Showing of photos/videos of old places/ celebrities via IVR for guessing, comparison, and discussion. Level2:Showing childhood/teenage photos of the participants via IVR for guessing, comparison and discussion.	Level 1: Showing of photos/videos of old places/ celebrities for guessing, comparison, and discussion. Level2:Showing childhood/teenage photos of the participants for guessing, comparison and discussion.
9	Categorizing objects	Level 1: Verbal fluency of different concepts/ semantic categories with cues provided via IVR. Level 2: Object categorization using different strategies with cues provided via IVR.	Level 1: Verbal fluency of different concepts/ semantic categories Level 2: Object categorization using different strategies

This table summarizes a few themed activities of the IVR-CST and conventional CST sessions.

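### Session 9 practises semantic category fluency, a primary outcome, in both arms, so within-arm fluency gains may partly be practice; the session 9 cue wording also needs reconciling

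*Protocol article*

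**What the plan says.** In the protocol article, *Outcome measures and procedures* numbers three primary outcomes. The last is "3) Verbal fluency of semantic category", scored as follows: "The number of items correctly produced in one minute in different semantic categories (animals, fruits, and transportation) will be tested". The same section treats fluency as a marker of semantic integrity, cognitive flexibility and executive function.

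Table 1, under *Treatment materials and procedures*, describes session 9 (categorizing objects). For IVR-CST it lists "Level 1: Verbal fluency of different concepts/ semantic categories with cues provided via IVR" and "Level 2: Object categorization using different strategies with cues provided via IVR". For conventional CST it lists "Level 1: Verbal fluency of different concepts/ semantic categories Level 2: Object categorization using different strategies".

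The text of that section says of each session that "two activities with varying levels of difficulty will be available to allow some flexibility". On how the arms compare it says: "In the conventional CST group, the same treatment activities, materials, and procedures will be used, while photos, pictures, or real objects will be presented".

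The aims ask two separate efficacy questions: whether IVR-CST improves cognition, and whether it does so more than conventional CST. The abstract accordingly plans both before/after and between-group comparisons.

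**The concern.** A therapy activity and a primary outcome are the same kind of task. If participants practise producing members of semantic categories and are later scored on doing so, a higher score can come from familiarity with the task, or with particular category members, without any wider cognitive change. The outcome would then support the first efficacy question less well than its primary status suggests.

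The second issue is how the arms are described. Table 1 attaches cues to both session 9 levels for IVR-CST and to neither for conventional CST, while the text presents the arms as using the same activities, materials and procedures. If the arms do differ in cued practice of a task that is later scored, the between-arm fluency contrast is no longer a contrast of delivery medium alone.

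**Working it through.** The plan gives no figure on this point, so there is none to reproduce. The check compares the passages and then adds one illustration on assumed values.

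**1. Task against outcome.** The outcome is semantic category fluency, counted over one minute in three named categories. Session 9 Level 1 is verbal fluency over semantic categories, in both columns of Table 1. The type of task is the same. Whether the categories are the same is not stated: Table 1 names none for session 9.

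**2. Timing and dose of practice.** *Assessment and treatment schedule* gives 14 sessions, two per week, in weeks 2 to 8, with assessments in weeks 1, 9 and 13. Sessions 1–2 fall in week 2, 3–4 in week 3, 5–6 in week 4, 7–8 in week 5 and 9–10 in week 6. Session 9 is therefore about 9 − 6 = 3 weeks before the first post-therapy test and 13 − 6 = 7 weeks before the last. It is 1/14 = 7.1% of sessions, and fluency is one of its two optional levels. Table 1 shows only a few sessions, so the others cannot be judged either way.

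**3. Which comparison is exposed.** Write the mean fluency change in an arm as C + P, where C is the gain in cognition and P the gain from practising the task.

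- Within IVR-CST, the observed change is C(IVR) + P(IVR). There is no untreated arm, so the design cannot separate the two terms.
- Between arms, the observed difference is [C(IVR) − C(conv)] + [P(IVR) − P(conv)]. If both arms practise alike, the second bracket is zero and practice cancels. It remains only if practice differs between arms, for example through cueing.

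**4. The cue wording.** Comparing the two columns of Table 1 row by row:

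- Session 6: the conventional text is the IVR text with the mention of IVR removed; the activity is unchanged.
- Session 2, Level 2: the VR delivery phrase is replaced by an on-site equivalent.
- Session 9, both levels: the whole cue phrase is gone, not only the mention of IVR.

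The pattern in sessions 2 and 6 would lead one to expect that cues common to both arms would still be mentioned in the conventional column. Against that, the text says photos, pictures or real objects are presented in the conventional arm, and these could serve as cues. Both readings remain open.

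**5. Illustration only.** The shifts below are assumptions, and the article gives nothing from which to estimate them. The test is a simple two-sided t-test at .05, not the planned model. Arm size is 66/2 = 33, or 33 × 0.75 = 24.75, about 25, after the 25% attrition allowed for. With no true effect and a standardized shift b, the noncentrality is b√n for change within one arm and b√(n/2) between arms. The chance of p < .05 for n = 25 to 33 per arm is:

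| Assumed b | Within one arm (practice only) | Between arms (cueing difference only) |
|---|---|---|
| 0.1 | 7.7–8.6% | 6.4–6.9% |
| 0.2 | 16.1–20.0% | 10.7–12.6% |
| 0.3 | 30.2–38.7% | 18.0–22.5% |

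The nominal rate is 5%. The between-arm column applies only if cueing really differs.

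**The case against.** The strongest reply is that the overlap is slight and partly inherent. CST is meant to stimulate language and executive function, so some of its activities will resemble measures of those functions. Fluency is one of two optional levels in one of 14 sessions, and a group that uses Level 2 would do categorization instead. Table 1 gives examples only, and category lists would normally sit in the therapy manuals, which are not shown. This stands as a limit on strength: the most one can say is that gains may partly reflect practice. It does not remove the point, because the match in task type is explicit in the article and no comparator separates practice from cognition within an arm.

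A reader might infer more in four ways, none of which the article supports.

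- *Practice biases the between-arm comparison.* The fluency activity is listed for both arms, so practice alone does not.
- *Unequal cueing is established.* No sentence says conventional participants receive no cues. The statement that the arms share activities, materials and procedures goes on to describe visual and physical stimuli for the conventional arm. Cues delivered through IVR may also simply be part of the intervention being compared.
- *The scored items themselves are rehearsed.* The article does not say that animals, fruits or transportation appear in therapy. It only does not exclude them.
- *The distortion is as large as the planned effect.* One might assume 1–2 extra words per category against an SD of 4–5, that is 1/5 = 0.2 to 2/4 = 0.5 SD, and set this beside d = 0.40. Neither the words nor the SD come from the article. The shift would describe practice that both arms receive, and the 0.40 was taken from global cognition, not fluency.

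**Conclusion.** The point holds in a limited form. Within-arm fluency change, which bears on whether IVR-CST improves cognition, may partly reflect practice at the scored task. The between-arm fluency contrast is affected only if cueing, or the amount of fluency practice, differs between arms; the article leaves the cueing question ambiguous.

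The point concerns one of three numbered primary outcomes; the sessions shown in Table 1 contain no matching rehearsal of digit span or of the HK-MoCA total. Its size cannot be derived from the article, and the rejection rates in the illustration depend wholly on the assumed shifts. The conclusion that practice cancels between arms assumes that both arms use the fluency level about equally often.

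Nothing here requires fluency to be removed from the primary outcomes. This is an inexpensive improvement, not a flaw that undermines the trial.

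**What to change.** 1. State that animals, fruits and transportation are kept out of the session materials of both arms. Alternatively, test fluency at weeks 1, 9 and 13 on categories never used in therapy.
2. Reconcile session 9 of Table 1 with the statement that both arms use the same activities, materials and procedures. Say whether conventional participants also receive cues and in what form, or that cueing is an intended part of the IVR condition.
3. Say that within-arm fluency change will be interpreted as possibly practice-related.

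The cost is a few sentences and a slightly narrower choice of session categories, provided it is done before the materials are finalised. Sample size, schedule and analysis model are unaffected.

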### Data analysis

Primary and secondary outcomes will be scored by a trained research assistant who is not involved in the assessment. To further reduce observer bias, a random code will be given to the scoring forms and audio-recording so that the research assistant will be blind to the identity of the participant, the experimental group assigned, and the timepoint of assessment. A linear fixed-effect model will be used to evaluate the participants’ performance in the outcome measures, as this statistical model is better in handling repeated observations, missing data, and individual variability [33]. Both time points (week 1/9/13) and conditions (IVR-CST vs. conventional CST) will serve as fixed factors, and scores of primary/secondary outcomes as dependent variables. Participants’ characteristics, such as age, baseline cognitive performance, and education, will be included in the model as covariates. Any significant main effects or interactions will be investigated via post-hoc analyses. Measurements concerning feasibility and user experience will be evaluated descriptively. In addition, a narrative summary of responses collected during the post-therapy interview will be reported.

For exploratory outcome, a 5-minute sample will be extracted from each participant and session from the IVR-CST group. To study possible changes in eye movement across sessions, the aforementioned eye-tracking parameters, including number of fixations, duration of fixation, and number of revisits on the AOI generated by each participant, will be evaluated by linear fixed-effect models as dependent variables, with session number as a fixed factor. Any significant main effects will be followed by post-hoc analyses. To investigate the possible associations between eye movement and treatment outcome, the correlation between the averaged difference in number and duration of eye fixations of each participant in the first and last three IVR-CST sessions and the difference score of HK-MoCA before and immediately after therapy will be analysed. If the correlation reaches statistical significance, multiple regression will be conducted, with the eye-tracking parameters as predictors, while the difference score of HK-MoCA pre/post therapy will serve as the predicted variable.

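### Both repeated-measures models are called fixed-effect and list no participant term, which contradicts the reason given for choosing them

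*Protocol article*

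**What the plan says.** Everyone is measured repeatedly: "All participants will be assessed at three time points throughout the study: week 1, week 9, and week 13" (Protocol article, Assessment and treatment schedule). In the IVR-CST arm, eye movements are also sampled in each of up to 14 sessions.

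For the primary and secondary outcomes, the Data analysis section says "A linear fixed-effect model will be used to evaluate" performance on these measures, because "this statistical model is better in handling repeated observations, missing data, and individual variability". It then lists the terms: "Both time points (week 1/9/13) and conditions (IVR-CST vs. conventional CST) will serve as fixed factors" and "Participants’ characteristics, such as age, baseline cognitive performance, and education, will be included in the model as covariates". On testing it says "Any significant main effects or interactions will be investigated via post-hoc analyses".

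The eye-tracking parameters "will be evaluated by linear fixed-effect models as dependent variables, with session number as a fixed factor".

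Neither description mentions a participant effect, a random effect or a within-person covariance. The section does not say which score serves as baseline cognitive performance.

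**The concern.** The model named and the reason for naming it do not fit together. Allowing for repeated observations and individual variability needs a participant effect or a within-person covariance. A linear model with only the listed factors and covariates has neither. It would treat up to 66 × 3 = 198 outcome rows, and up to 33 × 14 = 462 session rows, as independent.

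The consequences differ by test:

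- **Condition main effect.** This compares people, so its standard error comes out too small.
- **Condition-by-time contrast.** This compares changes within people, so its standard error comes out too large. It is also the contrast that answers whether IVR-CST is more efficacious than conventional CST.

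Because any significant main effect goes on to post-hoc analysis, a spurious condition effect would be followed up while a real difference in change could be missed. The Discussion already concedes that the small sample reduces power.

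**Working it through.** **Inputs.** From the Protocol article: 66 participants, 1:1 allocation, 3 visits, up to 14 sessions, 25% attrition, d = 0.40, 80% power, α = 0.05. Completers are 66 × 0.75 = 49.5, about 25 per arm. The article gives no within-person correlation r, so r is assumed: 0.5 to 0.7 for the main figures, 0.3 to 0.8 for the range. Scores have SD 1 and equal correlation between visits.

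**1. The plan's own figure.** The article does not name the test behind 66. A two-sided paired t-test with d = 0.40 needs 52, and so does a 2-group by 2-time interaction with f = 0.20 and r = 0.5. Then 52 × 1.25 = 65, or 66 for equal arms. An independent two-sample comparison needs 200 (two-sided) before attrition. Of the calculations tried, only those using within-person correlation reach 66, so an analysis that ignores it would not match.

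**2. Outcome model with the outcome's own week-1 score as covariate.** The single fitted slope is the average correlation of the three visits with week 1, b = (1 + 2r)/3. The pooled residual variance is 1 − b². The ratios of model SE to true SE are:

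- condition main effect: √[(1 + b)/(3b)]
- week-9 condition-by-time contrast: √[(1 − b²)/(1 − r)]

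Type I error is 2Φ(−1.96 × ratio).

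| r | b | Main-effect ratio | Type I | Interaction ratio | Type I |
|---|---|---|---|---|---|
| 0.5 | 0.667 | 0.913 | 7.4% | 1.054 | 3.9% |
| 0.7 | 0.800 | 0.866 | 9.0% | 1.095 | 3.2% |

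Simulation with 25 per arm agrees: about 7% and 9–10% for the main effect, 3–4% for the interaction. Over r = 0.3 to 0.8 (simulated with 33 per arm) the ranges are about 6–10% and 5–3%.

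**3. Power for a 0.4 SD interaction, 25 per arm, same covariate.** The true SE is √[4(1 − r)/25], or 0.283 at r = 0.5 and 0.219 at r = 0.7. The model SE is √[4(1 − b²)/25], or 0.298 and 0.240.

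- Correct change-score test: Φ(0.4/0.283 − 1.96) = 29%; Φ(0.4/0.219 − 1.96) = 45%, quoted as 44% below to match the simulation.
- Model as written: Φ[(0.4 − 1.96 × 0.298)/0.283] = 26%; Φ[(0.4 − 1.96 × 0.240)/0.219] = 37% (38% by simulation).

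**4. Outcome model when the covariate gives no such adjustment.** This is the limiting case of a baseline score unrelated to the outcome. The ratios become √[1/(1 + 2r)] and √[1/(1 − r)].

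| r | Main-effect ratio | Type I | Interaction ratio | Type I |
|---|---|---|---|---|
| 0.5 | 0.707 | 16.6% | 1.414 | 0.6% |
| 0.7 | 0.645 | 20.6% | 1.826 | 0.04% |

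The interaction model SE is √(4/25) = 0.40, so power at 0.4 SD is Φ[(0.4 − 0.784)/0.283] = 9% at r = 0.5 and Φ[(0.4 − 0.784)/0.219] = 4% at r = 0.7. A baseline score only partly related to the outcome falls between steps 2 and 4.

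**5. Eye-tracking session model.** Session number varies only within person, so the only ratio that applies is √[1/(1 − r)], which exceeds 1. Simulation with 33 people and 14 sessions gives type I error of 0.4% at r = 0.3 and no rejections in 3,000 runs at r = 0.5 or 0.7. With a participant term it is about 5%.

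**6. Eye-tracking and HK-MoCA.** The planned correlation and follow-on regression use difference scores, one set per participant. There are no repeated rows, so this defect does not reach them.

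**The case against.** The best defence is that this is a naming slip. The stated rationale describes a mixed-effects model, and an article may list only the fixed part and leave the random part and covariance to a fuller document. That is plausible, and the text does not show that the analysts intend to treat visits as independent. It does not remove the point. The article goes beyond leaving the random part unstated: it positively names a different model, twice, and readers will check the eventual analysis against that name. Reading the phrase as participant fixed effects does not rescue it either, because participant indicators would absorb condition, age, education and baseline score, all of which are listed as terms.

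A second objection is about size. A reader might take the worst figures, a main-effect type I error near 20% and interaction power near 4%, as the expected result. The documents do not support that, because a baseline cognitive covariate is in the model. If it is the outcome's own week-1 score, the distortion is moderate (steps 2 and 3). Since the score is not identified, and there are several primary outcomes, that protection is likely but not assured.

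A reader might also infer that every eye-tracking result is invalid, or wrong in both directions. Steps 5 and 6 show otherwise: the session test errs one way only, and the association with outcome is untouched. The eye-tracking analysis is also labelled exploratory.

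**Conclusion.** The point holds as a contradiction in the text: the model name and listed terms cannot do what the rationale claims, in the outcome model and in the eye-tracking session model. It does not establish that the final analysis will be wrong.

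Run as written at r = 0.5 to 0.7, with the outcome's own baseline as covariate, type I error is about 7–10% for the condition main effect and 3–4% for condition by time. Interaction power at 0.4 SD with 25 per arm is about 26–38%, against 29–44% for a correct change-score test. Without effective baseline adjustment the type I errors are about 16–20% and 1% or less. The eye-tracking session test has type I error of about 0.5% or less at r = 0.3 to 0.7.

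The sizes rest on the assumed correlation, equal correlation between visits and complete data. For any positive correlation of this kind the direction of the error does not depend on its value, although with the outcome's own baseline as covariate the distortion is negligible at r = 0.3.

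**What to change.** In both model descriptions in Data analysis, replace the term *linear fixed-effect model* with *linear mixed-effects model with a random intercept per participant (or a stated within-participant covariance)*. Keep the fixed factors and covariates already listed. In the same edit, say which score is meant by baseline cognitive performance for each outcome. The estimation method (such as REML) and the degrees-of-freedom method can be left to the statistical analysis plan.

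The cost is one sentence in each description and notice of the amendment to the bodies that the article already undertakes to inform. Data collection, sample size and participants are not affected.
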